## Study design

A substudy of SATISFY-SOS, this prospective cohort study will synthesise three sources of information:
Preoperative ‘baseline’ survey—completed by patient at the preoperative assessment clinic within 4 weeks of surgery.Postoperative ‘30-day’ and ‘1-year’ surveys—completed by patients ∼30 days and 1 year following surgery, respectively.Electronic medical record—provides additional demographic and medical data.

The surveys were developed following a consultative process, including people with relevant expertise. The guiding principle was to formulate a survey that would be meaningful, reliable and practical for widespread dissemination to an unselected patient population. All surveys are available in the online supplementary material.

10.1136/bmjopen-2016-011570.supp2Supplementary data

## Study groups

The target population for this study is patients who underwent preoperative assessment for elective surgery at Barnes Jewish Hospital in St. Louis, Missouri between 16 January 2014 and 7 October 2015. Over 70% of patients undergoing elective surgery are assessed by the centre for preoperative assessment and planning (CPAP) clinic before surgery. Reasons for no assessment include urgent surgery, geographical limitations or surgeon preference. Inclusion criteria include age 18 or older, ability to read the English consent form, ability to consent and plans to undergo elective surgery. During the analysis phase, patients are excluded from participation in SATISFY-SOS if they have undergone surgery within 60 days of their planned surgery date.

Approximately 65% of all eligible patients consent to participate in the study. Reasons for non-participation include patient refusal (∼70% of cases), lack of nurse time or training (∼20%), or lack of English literacy (∼10%). A study comparing participants to non-participants showed no major differences in characteristics.^19^ Approximately 92% of all consented patients complete a baseline survey. Reasons for lack of complete participation include insufficient time or changing their mind. Overall, the estimated number of eligible patients per YEAR is 15 500, the estimated number of consenting patients per year is 10 000, and the estimated number of baseline survey records per year is 9200. Approximately 16 000 baseline survey records are available in the time period specified for this study (16 January 2014 to 7 October 2015).

For the purposes of this substudy, only the first complete record for each patient (ie, baseline survey and corresponding 30-day survey) will be included in the final data set (∼94% of the available records). This practice ensures that each record is statistically independent from all the other records.

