## Specific aims

*Aim 1*: Describe characteristics of postoperative falls in an unselected surgical population, including their rate, timing, associated injuries and risk factors.

We hypothesise that the occurrence, injuries and risk factors of postoperative falls will be similar to those of preoperative falls, and the rate of postoperative falls will decline from 30-days after surgery to 1 year after surgery.

*Aim 2a*: Determine whether a preoperative history of falls serves as a useful tool for predicting falls in the 30 days (primary outcome) and 1 year following surgery of all types.

*Aim 2b*: Determine whether a preoperative history of falls predicts patient-centred outcomes including functionality and quality of life at 30 days and 1 year after surgery (secondary outcomes).

*Aim 2c*: Replicate findings that a preoperative history of falls predicts in-hospital surgical complications and readmission at 30 days (secondary outcomes).

We hypothesise that a history of preoperative falls will predict poor postsurgical outcomes, including postoperative falls, functional dependence, poor quality of life, in-hospital complications and readmission.

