## Recruitment

Nurses at the CPAP clinic assess patient eligibility, recruit patients to participate, and obtain written consent using the consent form found in the online supplementary material. This consent form serves as the source of patient information for the study. While most patients decide whether or not to participate at this time, a patient can decide to participate any time between his or her CPAP visit and his or her surgery day. For patients who need special assistance, such as those who are blind or cannot physically sign a form, a witness can be obtained. However, in practice, this rarely occurs. No arrangements are made for non-English speakers, mentally ill, children, or those suffering from dementia since those are excluded groups (see the Study groups section). Patients receive no compensation for participation. If patients agree to participate, the CPAP nurse asks them to complete a brief baseline survey at the time of consent. Approximately 30 days and 1 year following surgery, they receive similar follow-up surveys. Both surveys were designed to take 10–15 min to complete. The SATISFY-SOS research team holds monthly update meetings with all CPAP nurses to inform them about study progress and to encourage optimal recruitment.

10.1136/bmjopen-2016-011570.supp3Supplementary data

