## Data

### Data to be collected

Incomplete follow-up is a major source of bias in many long-term observational cohort studies. To maximise completeness of 30-day and 1-year follow-up data, the following sequence of contact methods is performed. First, the survey is emailed up to three times starting ∼20 days after the surgery date. For those who did not provide an email or who do not respond to the emails, a paper survey is also mailed 25 days after the surgery date. If a patient does not respond to the first paper survey, a second paper survey is mailed 21 days later. If the second paper survey is not returned, the patient is phoned up to five times. Using this aggressive protocol, the 30-day survey response rate between 16 January 2014 and 7 May 2015 was ∼55%. An identical process occurs for the 1-year survey, beginning 365 days after the surgery date. For the date ranges included in this study, two versions of the 30-day survey (V.2 and V.3) and two versions of the 1-year survey (V.1 and V.2) were administered to participants. See online supplementary material to view these surveys.

10.1136/bmjopen-2016-011570.supp4Supplementary data

10.1136/bmjopen-2016-011570.supp5Supplementary data

10.1136/bmjopen-2016-011570.supp6Supplementary data

10.1136/bmjopen-2016-011570.supp7Supplementary data

Access to the SATISFY-SOS data is limited to investigators and staff who: have access to the Department of Anesthesiology desktop computers, have a computer account with the Department of Anesthesiology, use an IP address from within the department offices, have written permission to analyse the data from the principal investigator, and have authorised access to the database. For this project, the investigators formulated a list of requested data. They will provide that list to the informaticist, who manages the SATISFY-SOS database and has access to other medical records data. Using queries in MetaVision (iMDsoft, Needham, Massachusetts, USA), the informaticist will provide the requested survey and medical record data to the investigators. The query start date will be 16 January 2014 since important survey revisions occurred before this date.

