## Statistical considerations

### Sample size calculations

The required sample size is calculated based on the primary outcome, which is a fall within 30 days of surgery. Appropriate logistic regression models contain at least 10 ‘events’ per predictor variable.^20^ Since our prespecified model for postoperative falls includes 13 dependent variables (see the Analysis section), a sample with at least 130 events is required. In our population, preliminary work shows that ∼10% of patients report falling in the month following surgery. Thus, the minimum sample size needed for this study is 1300 patients.

Currently, our database contains over 9000 complete records (ie, baseline and 30-day survey) after the 16 January 2014 start date. To meet statistical assumptions of independent observations, we estimate that ∼600 records from patients with at least one previous entry in the data set will be excluded. We estimate that an additional 600 records will be excluded due to inappropriate time intervals (baseline survey to surgery <0 or >59 days; surgery to 30-day survey <20 or >120 days; or surgery to 1-year survey <275 or >455 days). Thus, our final sample size will be ∼7800.

Within this final sample, two versions of the 30-day (V.2 and V.3) and 1-year surveys (V.1 and V.2) were administered. Only V.3 of the 30-day survey and V.2 of the 1-year survey contain a validated falls question, as recommended by the Prevention of Falls Network Europe consensus group.^21^ The difference in question phrasing caused statistically significant differences in the percentage of patients reporting postoperative falls (5.5% vs 10% at 30 days and 18% vs 28% at 1-year, p<0.001). Out of the available records, about 20% (1500) completed V.3 of the 30-day survey, which is more than the 1300 required for the primary outcome. Thus, to maximise outcome validity, only these versions will be used for postoperative falls. In contrast, the readmission question contained only minor differences (‘Were you readmitted to the hospital?’ for V.2 vs ‘Check all that apply […] admitted to a hospital’ for V.3). The percentage reporting readmission was similar between surveys (5.2% vs 5.7%, p=0.416), so the results from both versions will be combined. The remaining outcomes were identical and will use all available data from both versions of the 30-day and 1-year surveys.

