## Limitations

This study contains several important limitations. First, the patients included in this study may represent a non-generalisable sample of the entire preoperative population. This study includes just one academic medical centre, and its patient population and rules for preoperative assessment clinic attendance may differ from that of other hospitals. In addition, only 65% of eligible preoperative assessment clinic attendees enrolled in the study, which may introduce bias. However, our analyses indicate that participants do not differ in important ways from non-participants. Furthermore, even if the sample was maximally biased, enrolling 65% of the actual target population means the results contain at least 80% accuracy.^28^ Another factor that biases the sample is non-response to the follow-up surveys. Although we mitigated non-response through an extensive follow-up protocol, only 55% of patients complete a 30-day survey.

The surveys also introduce several limitations. While the surveys are entitled ‘30-day’ and ‘1-year’ surveys, and most surveys occur near these times, the dates actually range from 20 to 120 and 275 to 455 days following surgery, respectively. In addition, each survey has two versions. Most questions are similar (readmissions) or identical (functional dependence, quality of life, complications) and can be combined. However, the postoperative falls question is significantly different. We will exclude results from the non-validated version, reducing the sample size available for this question. All important confounders will still be included, but the model may not have a sufficient number of outcomes to test all of the interactions of interest. Since many published papers do not test interactions, we do not think this compromises the robustness of the model.

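### The single entry rule limits every 1-year analysis to patients who returned a 30-day survey, although no 1-year model needs one

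*Protocol article*

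**What the plan says.** Study groups fixes one data set for the whole substudy: "only the first complete record for each patient (ie, baseline survey and corresponding 30-day survey) will be included in the final data set". The reason given there is that records should be statistically independent.

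Sample size calculations uses the same definition, "our database contains over 9000 complete records (ie, baseline and 30-day survey) after the 16 January 2014 start date", and deducts from that count to reach a final sample of about 7,800. It then describes the two 1-year survey versions as lying within that final sample. No separate inclusion rule for 1-year outcomes appears.

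The 1-year outcomes are nevertheless part of the aims. Aim 2a concerns "predicting falls in the 30 days (primary outcome) and 1 year following surgery of all types", and Aim 2b covers functionality and quality of life at both times. The Analysis section lists 1-year models for falls, the Barthel Index and both quality-of-life scores.

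On follow-up, Recruitment says of participants that "Approximately 30 days and 1 year following surgery, they receive similar follow-up surveys". Data to be collected adds that "An identical process occurs for the 1-year survey, beginning 365 days after the surgery date". Neither section makes the 1-year contact depend on a 30-day reply.

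**The concern.** A 1-year outcome adjusted for baseline variables needs a baseline survey and a 1-year survey. Under the rule as written, a patient who has both but did not return the 30-day survey never enters the data set.

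Two things are at stake for the 1-year parts of Aims 1, 2a and 2b. Usable outcome data may be set aside. The 1-year sample also becomes conditional on responding twice, with the first condition imposed by the plan and not by the missing outcome itself. If failure to answer at 30 days goes with poor early recovery, which is plausible but not shown, the rule would tend to remove patients in whom the hypothesis is of most interest.

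**Working it through.** **1. Reproduce the stated sample.** Sample size calculations gives over 9,000 paired records, about 600 repeat-patient exclusions ("600 records from patients with at least one previous entry in the data set will be excluded") and about 600 timing exclusions.
- 9,000 − 600 − 600 = 7,800, as stated.
- (9,000 − 600)/9,000 = 93.3%, against the roughly 94% retained in Study groups. By contrast, 9,000/16,000 = 56%. The available records in Study groups are therefore already baseline/30-day pairs.

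The 7,800 consists of 30-day responders only. No stated number is wrong; the issue is who can enter.

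**2. Does any 1-year model need the 30-day survey?** I compared the covariate lists under Analysis with the sources and time points in Table 1.
- Common to all models: age, sex, race, BMI, preoperative falls, Charlson Index, ASA status and procedural cardiac risk. All are collected at baseline or surgery.
- Falls: activity level, altered elimination, mobility, dizziness and depression. All baseline.
- Barthel decline: baseline Barthel, neurological impairment, mood disorder and smoking. All baseline.
- Quality of life: the baseline score, chronic pain and mood disorder, plus activity level and smoking for the physical score. All baseline.
- The only covariate from the 30-day survey is in-hospital complications, in the readmission model, and readmission is itself a 30-day outcome.

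So no 1-year model uses 30-day data.

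**3. Share of baseline records barred.** Study groups says "16 000 baseline survey records are available in the time period specified for this study", and Limitations says "only 55% of patients complete a 30-day survey".
- From the response rate: 16,000 × (1 − 0.55) = 7,200, or 45%.
- From the record count: 16,000 − 9,000 = 7,000, or 44%.

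**4. How many 1-year surveys that could mean.** The article gives no 1-year response rate, so what follows is assumption.
- *Share of the cohort at day 365.* The window from 16 January 2014 to 7 October 2015 is 629 days. The Introduction estimates study dates of March to June 2016. With even accrual, and the assessment date taken as the surgery date, patients seen by 2 March 2015 (410 days) had reached day 365 by 1 March 2016: 410/629 = 65%. Those seen by 1 July 2015 (531 days) had reached it by 30 June 2016: 531/629 = 84%.
- *Response among 30-day non-responders.* Assumed 10% to 30%.
- Low end: 7,000 × 0.65 × 0.10 = 455, or 468 with 7,200.
- High end: 7,200 × 0.84 × 0.30 = 1,814, or 1,764 with 7,000.

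The result is roughly 500 to 1,800 surveys before timing and version exclusions. Fewer would count for 1-year falls, because only V.2 of the 1-year survey is used for that outcome.

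**5. As a share of all 1-year surveys.** With response *a* in 30-day responders and *c* in non-responders (both assumed), the share left out is 7,200*c*/(8,800*a* + 7,200*c*). If both groups reach day 365 alike, the accrual fraction cancels.
- *a* = 0.75, *c* = 0.10: 720/7,320 = 9.8%.
- *a* = 0.70, *c* = 0.20: 1,440/7,600 = 18.9%.
- *a* = 0.65, *c* = 0.30: 2,160/7,880 = 27.4%.

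**The case against.** **The sentence is mainly a de-duplication rule in a condensed article.** Its stated purpose is independence, and a fuller plan might define sets by outcome. The same section also says that the remaining outcomes use all available data from both survey versions. In context, though, that phrase is about pooling versions within the final sample, not about who enters it. The paired definition appears twice and generates the 7,800. If the authors meant otherwise, the text still needs correcting.

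**The lost surveys are not documented.** This stands. The article describes a separate 1-year contact sequence with no stated condition on 30-day response. It does not say that 30-day non-responders were contacted, and it counts no returns from them. A reader might infer that thousands of valid 1-year surveys are known to be thrown away. That would treat all 16,000 baseline records as having reached one year, and at the top end would need 1-year response to be independent of 30-day response. The article supports neither.

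**Bias is not shown.** This also stands. Distortion of the association between preoperative falls and a 1-year outcome would require 30-day response to depend on exposure and outcome beyond the adjusted baseline variables. Any remedy still conditions on 1-year response.

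**Non-response is already acknowledged.** Limitations names the 55% response as a source of bias, and Analysis plans a comparison of 30-day responders with non-responders. Neither tells the reader that the 1-year results depend on 30-day response, and neither restores the excluded data. Multiple imputation fills variables in admitted records; it admits no one.

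**A common cohort helps the hypothesis that the fall rate declines from 30 days to 1 year.** This has some force, since different samples mix change over time with change in composition. But no paired 30-day/1-year analysis is planned, and falls already use a different version-restricted sample at each time. A sensitivity analysis can meet the point.

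**Conclusion.** The concern holds for the 1-year analyses. As written, the entry rule confines them to 30-day responders, bars about 44% to 45% of baseline records, and serves no purpose in those models, since one record per patient already secures independence.

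The number of 1-year surveys forgone is not derivable. The range of roughly 500 to 1,800 rests on three assumptions: 10% to 30% response at 1 year among 30-day non-responders, even accrual, and a data extract between March and June 2016. That any such surveys exist is an inference from the contact procedure.

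A reader might go further and conclude that the 1-year associations are biased. The article supports only that bias is possible, with size and direction unknown. The primary outcome and the other 30-day outcomes are untouched. The point is worth correcting before analysis but does not threaten the main result.

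**What to change.** Define the analysis set by outcome time, with one record per patient in each:
- 30-day outcomes: the first eligible record with a baseline survey and a valid 30-day survey.
- 1-year outcomes: the first eligible record with a baseline survey and a valid 1-year survey, whether or not a 30-day survey was returned.

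State whether 30-day non-responders were contacted at 1 year, and how many replied. Add a comparison of 1-year responders with non-responders to the one already planned at 30 days. Report the 1-year results in patients with both surveys as a sensitivity analysis; this also keeps a common cohort for comparing fall rates at 30 days and 1 year.

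The cost is one changed selection rule in the data query, the matching protocol wording and one extra comparison. No new data collection is needed. The article says analysis starts only after the protocol is accepted, so the change can still be prespecified. The downside is two denominators in the flow chart and samples that are not fully nested.

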Table 1 contains all variables to be collected for the study, along with the form of the variable, its source, time point for collection and whether or not it comes from a standardised tool. Of note, the informaticist performs rigorous data validation on each queried variable. If continuous variables are found to exhibit non-linearity, they will be categorised in accordance with their distribution.

**Table 1 BMJOPEN2016011570TB1:** Characteristics of all variables used in this study

Type	Variable name	Form	Source	Time	Use of standardised tool
Explanatory	Preoperative falls	0, 1, 2, 3+	Survey	BL	Yes^21^
	Charlson Comorbidity Index	Ordinal, 0–12	CPAP H&P	BL	Yes^29^
	ASA physical status	Ordinal, 1–6	Anaesthesia record	Surgery	Yes^30^
	Procedural cardiac risk	Ordinal, 5 categories from high to low	CPAP clinician	BL	Yes^31^
Outcome	Postoperative falls	Binary (V.2); 0, 1, 2, 3+ (V.3)	Survey	30 days, 1 year	Yes^21^
	Functional dependence	Ordinal, 0–100 by 5	Survey	30 days, 1 year	Yes^32^
	Physical quality of life	Continuous, 0–100	Survey	30 days, 1 year	Yes^33^ ^34^
	Mental quality of life	Continuous, 0–100	Survey	30 days, 1 year	Yes^33^ ^34^
	In-hospital complications	Dichotomous	Survey	30 days	No
	Readmission	Dichotomous	Survey	30 days	No
Demographic	Age	Continuous	Medical record	BL	NA
	Sex	Dichotomous	Medical record	BL	NA
	Race	Nominal	Medical record (patient report)	BL	NA
	Ethnicity	Hispanic/Latino or not	Medical record (patient report)	BL	NA
	Body mass index	Continuous	CPAP nurse	BL	Yes
Confounder	Functional dependence	Ordinal, 0–100 by 5	CPAP nurse	BL	Yes^32^
	Physical quality of life	Continuous, 0–100	Survey	BL	Yes^33^ ^34^
	Mental quality of life	Continuous, 0–100	Survey	BL	Yes^33^ ^34^
	Smoking status	Current, past, never	CPAP physician or nurse	BL	NA
	Physical activity level	<4, 4–6, 6–10, >10 (METs)	CPAP physician	BL	Yes^35^
	Incontinence	Dichotomous (any issue)	CPAP nurse	BL	Yes^32^
	Toileting difficulty	Dichotomous (any issue)	CPAP nurse	BL	Yes^32^
	Mobility issue	Dichotomous (any issue)	CPAP nurse	BL	Yes^32^
	Neurological impairment (stroke, paraplegia or quadriplegia, Parkinson disease or multiple sclerosis)	Dichotomous	CPAP H&P	BL	No
	Chronic pain	Dichotomous	CPAP physician ROS	BL	No
	Dizziness/vertigo	Dichotomous	CPAP physician ROS	BL	No
	Depression	Dichotomous	CPAP H&P	BL	No
	Anxiety	Dichotomous	CPAP H&P	BL	No
Descriptive	Fall-related injury	Check all that apply	Survey	BL, 30 days, 1 year	No

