### Analysis

To begin analysis, we will perform descriptive statistics of all variables used in the analysis, using means, SDs and Student's t-tests for normal, continuous variables; medians, IQRs and Mann-Whitney tests for non-parametric, continuous variables; and proportions and χ^2^ tests for categorical variables. We will explore and report differences between patients with follow-up surveys at 30-days compared with non-responders.^26^ Among patients included in the analysis, we will also explore and report differences between those with complete records versus those with missing data. For variables with missing data, we will perform multiple imputation where appropriate.

Our first aim is to describe the characteristics of postoperative falls in an unselected surgical population, such as their occurrence, timing, injuries and risk factors. To achieve that goal, we plan to perform the following analyses:
Descriptive statistics:
Per cent who fell while still in the hospital;Number of falls (0, 1, 2, 3+) and fall rate in the 30 days and 1-year following surgery;Fall rate and per cent who fell by surgery type (10 surgery departments);Injuries from falls in the 30 days following surgery;Injuries from falls in the 1 year following surgery.▸χ^2^:
Proportion with any injury, comparing preoperative falls to postoperative falls at 30 days and 1 year;Proportion with severe injury, comparing preoperative falls to postoperative falls at 30 days and 1 year.Risk factors: see results from logistic regression model in Aims 2a–c.

As a subaim of Aim 1, we also plan to explore the rate of falls in the short-term versus long-term postoperative periods. To accomplish this, we will calculate the rate of falls per 100 person-years in the Behavioral Risk Factor Surveillance System (BRFSS) system, which serves as the control rate of falling in the general population of adults in the USA. We will then convert the 30-day, 6-month and 1-year fall rates from the SATISFY-SOS population into falls/(100 person-years) using the BRFSS distribution. Finally, we will compare the observed rate of falling to the general population's rate of falling at 1 month and 1 year (Student's t-test) to estimate how the rate of falls changes after surgery.

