Presence or absence of at least one fall in the 30 days (primary outcome) and 1 year following surgery:
Physical activity level (<4 vs >4 metabolic equivalents (METs));Baseline altered elimination (bowel or bladder);Baseline mobility abnormality;Dizziness/vertigo;Depression.▸Barthel Index that is worse than baseline, at 30 days and 1 year after surgery:
Baseline Barthel Index score;Neurological impairment;Mood disorder (depression or anxiety);Smoking status.▸Physical quality of life score, at 30 days and 1 year after surgery:
Baseline physical quality of life score;Preoperative physical activity level (<4 vs >4 METs);Chronic pain;Mood disorder (depression or anxiety);Smoking status.▸Mental quality of life score, at 30 days and 1 year after surgery:
Baseline mental quality of life score;Chronic pain;Mood disorder (depression or anxiety).▸Presence or absence of any complication that occurred in the hospital, as reported in the 30-day survey:
Smoking status.▸Presence or absence of readmission at 30 days, as reported in the 30-day survey:
In-hospital complications (30-day survey);Incontinence.

After running each model, we will substitute the number of falls (0, 1, 2, 3+) explanatory variable for the falls and fall injuries composite scale^27^ to evaluate which scale better predicts outcomes. Since we test multiple hypotheses, the threshold for significance will be α=0.01. We will report results using ORs and 99% CIs, along with variance estimates for regression parameters.

Using SAS/STAT software, V.9.4 (SAS Institute, Cary, North Carolina, USA), [name] will perform all analyses. Analysis will begin only after acceptance of this protocol for publication. This approach reassures readers that key analyses were truly prespecified rather than post hoc. If the authors decide to perform post hoc analyses, these will be described as such and will be performed for the purpose of further hypothesis generation.

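### With no vital status collected, every survey outcome is conditional on survival and response, and an excess of deaths among fallers would go unseen

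*Protocol article*

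**What the plan says.** - **Entry rule (Study groups).** The article says that "only the first complete record for each patient (ie, baseline survey and corresponding 30-day survey) will be included in the final data set".
- **Who reports (Study design).** The follow-up surveys are "completed by patients ∼30 days and 1 year following surgery, respectively". The text describes no proxy route.
- **Source of outcomes (Table 1 and Analysis).** Table 1 gives the survey as the source of postoperative falls, functional dependence, both quality-of-life scores, complications and readmission. The outcome list in Analysis repeats this for two of them: "Presence or absence of any complication that occurred in the hospital, as reported in the 30-day survey" and "Presence or absence of readmission at 30 days, as reported in the 30-day survey". Function is defined as "Barthel Index that is worse than baseline, at 30 days and 1 year after surgery".
- **Variables (Data to be collected).** "Table 1 contains all variables to be collected for the study". Neither vital status nor date of death is among them, although the electronic medical record is one of the three data sources under Study design.
- **Survey windows (Sample size calculations).** Records are excluded for "surgery to 30-day survey <20 or >120 days; or surgery to 1-year survey <275 or >455 days".
- **Non-response and missing data (Analysis).** "We will explore and report differences between patients with follow-up surveys at 30-days compared with non-responders". Multiple imputation is planned where appropriate, with no exception for death. Limitations names non-response as a source of bias but does not mention death.

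**The concern.** Aim 2 asks whether a fall history, known before surgery, predicts how the patient fares afterwards, and the Justification section wants the answer to inform preoperative decisions. When those decisions are made, nobody knows who will survive. Under this plan a patient who dies of an in-hospital complication, or during a readmission, cannot be counted as having had either. Death has no value on the Barthel Index or the quality-of-life scales.

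The study starts from the idea that falls signal declining health, so death could well be related to the exposure. A result of no association with 1-year function could then coexist with more deaths among fallers, and nothing in the listed data would reveal it. The planned comparison of responders with non-responders does not help, because with the listed variables it cannot separate the dead from those who declined or were not reached.

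**Working it through.** **1. The plan's own record flow.** Sample size calculations starts from over 9000 complete records and removes about 600 repeat records and 600 with unsuitable intervals: 9000 − 600 − 600 = 7800, as stated. As a check, 16 000 baseline records × 0.55 response = 8800, close to 9000. The final 7800 is 7800 / 16 000 = 49% of baseline records, so any deaths lie inside a much larger group without usable follow-up.

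**2. Where a death goes.**

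| Time of death | 30-day outcomes | 1-year outcomes |
|---|---|---|
| Before the 30-day survey is returned (accepted up to day 120) | Patient not in the data set | Patient not in the data set |
| After the 30-day survey, before the 1-year survey | Kept | No survey; imputation not excluded |

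**3. How many (mortality assumed; the document gives none).** Applying the 94% first-record share to baseline records gives 16 000 × 0.94 ≈ 15 000 patients.
- Assumed 30-day mortality of 0.3% to 1%: 15 000 × 0.003 = 45 to 15 000 × 0.01 = 150 deaths.
- At 55% response, 45 × 0.55 ≈ 25 to 150 × 0.55 ≈ 83 of these would have been analysed had they lived.
- Non-responders number 15 000 × 0.45 = 6750, so these deaths would be 45 / 6750 = 0.7% to 150 / 6750 = 2.2% of them.
- Assumed mortality of 2% to 5% between the two surveys: 7800 × 0.02 = 156 to 7800 × 0.05 = 390 patients.

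**4. What survivor-only outcomes could hide.** Let d be mortality and p the outcome rate in survivors. The risk of death or the outcome is d + (1 − d)p. Take the same p in fallers and non-fallers, so that the survivor OR is 1.00. For function, p = 20%, the protocol's one-month figure borrowed for one year; for readmission, p = 5.5%.

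| Outcome | d, non-fallers / fallers | Risk of death or outcome | OR |
|---|---|---|---|
| Worse function | 1% / 2% | 0.208 / 0.216 | 1.05 |
| Worse function | 2% / 4% | 0.216 / 0.232 | 1.10 |
| Worse function | 3% / 6% | 0.224 / 0.248 | 1.14 |
| Readmission | 0.3% / 0.6% | 0.0578 / 0.0607 | 1.05 |
| Readmission | 1% / 2% | 0.0645 / 0.0739 | 1.16 |
| Readmission | 1% / 3% | 0.0645 / 0.0834 | 1.32 |

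Only the last row exceeds the 20% minimum important difference stated under Sample size calculations.

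**5. Direction.** Now let survivors show the protocol's own detectable increases: 12% for complications, 34% for readmission, 15% for function. Compare the survivor OR with the OR for death or the outcome, when fallers die at 1 to 3 times the rate of non-fallers.

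| Outcome | Mortality, non-fallers | Survivor OR | OR with death, ratio 1 | OR with death, ratio 3 |
|---|---|---|---|---|
| Complications | 1% | 1.17 | 1.17 | 1.25 |
| Readmission | 1% | 1.37 | 1.31 | 1.64 |
| Worse function | 5% | 1.20 | 1.16 | 1.67 |

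With equal mortality the OR including death is no larger than the survivor OR, and for readmission and function it is smaller; with higher mortality in fallers it is larger. The document does not say which applies.

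**The case against.** Much of the case on the other side stands.

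- **Ordinary non-response dominates.** About 45% do not return the 30-day survey. The protocol discloses this and plans to examine it. On the assumed mortality, deaths are at most about 2% of the non-responders.
- **Bias towards the null is not shown.** A reader might infer that the survivor analysis is biased that way. This requires fallers to die more often, and no figure in the document says they do.
- **Different question, not a wrong answer.** In step 4 an OR of 1.00 is correct for function among survivors. Death or worse function is another endpoint, and mortality is not among the stated aims. What the protocol lacks is a statement that it answers the narrower question, and the data to show what that leaves out.
- **Not every death is dropped.** A reader might take the complete-record rule to remove all deaths. It removes only those before the 30-day survey is returned; later deaths stay in the 30-day analyses.
- **The imputation sentence is qualified.** It says where appropriate, so imputation after death is not planned, merely not excluded.
- **The obvious remedy is flawed.** Exempting only the dead from the complete-record rule would add all deaths to about 55% of survivors. At 1% mortality, 150 deaths would join 14 850 × 0.55 ≈ 8170 living responders: 150 / 8320 = 1.8%, about 1.8 times the true rate.

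One argument does not succeed. The handling of deaths may be left to an analysis plan, but no analysis plan can use a variable that is not collected, and the article describes its variable list as complete. The parent study's database may hold vital status; if so, adding it is easier still.

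**Conclusion.** The point holds as one of interpretation and data collection. All postoperative outcomes are conditional on survival and on response, the listed variables cannot separate death from other non-response, and an excess of deaths among fallers could go unnoticed. This follows from the text and needs no assumption about mortality.

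Its size does depend on mortality, which the document does not give. At low mortality any effect is probably small, especially for complications with their 28% base rate. Readmission, at 5.5%, is the most sensitive. The function examples, with ORs of 1.05 to 1.14, stay below the protocol's own 20% threshold. The document does not support a claim that the planned results are materially biased, or in which direction, and no material effect on the primary outcome has been shown. This is a cheap improvement worth making before analysis begins.

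**What to change.** 1. Add vital status and date of death to the planned medical-record query, for every patient with a baseline survey.
2. Report 30-day and 1-year deaths by preoperative fall category, with all baseline patients (about 15 000) as the denominator.
3. In the comparison of 30-day responders with non-responders, split the non-responders into dead and alive.
4. State that no outcome will be imputed for a time after death.
5. State that the survey outcomes are conditional on survival.
6. If a sensitivity analysis of death or readmission, or of death or worse function, is added, do not add all deaths to the responders alone. Use the full baseline cohort, with living responders weighted for non-response, for example by inverse-probability weights from baseline variables.

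The cost is one or two fields in a query that has yet to be run, one table of deaths and a little more analysis. Deaths outside the health system may be missed, and the report should say so.
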